### Intervention group

The intervention will be provided in addition to usual care for a duration of six months. The intervention differs to usual care in terms of the mode, frequency and intensity of dietetic involvement. Dietitians will complete training in Behaviour Change Technique Taxonomy v1 (BCTT – V1) and all aspects of the intervention including symptom management, nutrition counselling, provision of oral nutrition supplement drinks, enteral nutrition regimen development and feeding tube management [30]. To reduce barriers to nutrition care, the nutrition intervention will be delivered via telehealth making it more widely accessible for a larger population, with the mode (telephone or videolink) determined by participant preference [21, 22]. Dietetic consultations will occur weekly at a minimum, as previous studies have displayed that consistent dietetic interactions can create a sense of support and rapport leading to greater engagement and disclosure of symptoms [21]. The intervention dietitian will contact participants as soon as practicable after randomisation to complete the initial nutrition assessment, and to arrange postage of a resource pack to participants. The pack contains an information booklet outlining key contacts, weight record templates, common side effects of treatment and how to manage them, and nutrition intervention strategies and education. The intervention dietitian will refer to the participant booklet during consultations, as a guide for dietary education and counselling. The booklet al.so outlines enteral feeding information including daily care of feeding tubes and a section to document individualised regimens for those that receive a tube. The participant can choose to record information in the booklet, such as medication changes or timing of symptoms, to report back to the intervention dietitian during weekly consults. Participants will also receive a diary to record PERT dosages, a PERT education booklet, and a pill box to store PERT capsules, as well as samples of oral nutrition supplement drinks to trial. Provision of trial supplement drinks will be tailored as required, depending on participants’ medical history e.g. participants with poorly controlled diabetes mellitus.

The intervention dietitian will assist with optimisation of participants’ oral intake and where relevant, use of a feeding tube for supplementary nutrition, each week for the duration of the six-month study period. Dietitian contact with the participant may occur more than once per week if the participant contacts the dietitian e.g. via phone or email with a query, or if there is an escalation in frequency or severity of nutrition impact symptoms.

#### Nutrition optimisation

Intervention dietitians will follow the Academy of Dietetics Nutrition Care Process of Assessment, Diagnosis, Intervention, and Monitoring/Evaluation (ADIME), as adopted by Dietitians Australia, for standardised dietetic care in all nutrition assessments and reviews [31, 32]. This process involves collection of information regarding anthropometry, biochemistry, clinical data, dietary intake, enteral nutrition (where relevant) and consumption of oral nutrition supplement drinks. Individualised nutrition requirements will be calculated using the European Society for Clinical Nutrition and Metabolism (ESPEN) guidelines for nutrition in cancer patients and adapted as required [33]. Diet histories will be quantified using the Easy Diet Diary App to determine total macronutrient and micronutrient intake [34]. Recommendations for oral nutrition supplement drinks and the need for supplemental enteral feeding will be based on adequacy of participants’ oral diet intake, determined using study developed ready reckoners. Reducing deficits in nutrition intake will be prioritised to achieve weight stability and improve nutrition status during treatment. Intervention strategies and goal setting may include the provision of oral nutrition supplement drinks, management of nutrition impact symptoms, dietary education including the utilisation of written education materials, dietary counselling where nutrition recommendations are based on participant’s reported intake and behavioural strategies from the BCTT – V1 and potential for escalation to enteral nutrition where appropriate [30]. Behaviour change techniques will be used to support goal setting e.g. problem solving and action planning. At each participant review, goal achievement will be assessed; goals can be ceased, modified, or continued in addition to the setting of new goals. Behaviour change techniques as described in the BCTT-V1 that are used in each participant interaction will be recorded [30].

#### Oral nutrition support

The intervention dietitian may recommend oral nutrition supplement drinks to help meet an individual’s requirements. The amount to consume each day will be discussed with the participant, aiming to reduce the energy and protein deficit and meet the individual’s nutritional needs. The oral nutrition supplement drinks available to participants are Vital^®^ 1.5, Ensure^®^ Compact 2.4, Ensure^®^ Plus, Resource^®^ Ultra and Resource^®^ Fruit Beverage which will be provided free of charge to participants. This range includes both fruit-based and milk-based options, a peptide-based formula and up to 17 different flavours, allowing greater choice for participants.

#### Enteral feeding

The intervention dietitian will utilise evidence-based guidelines from the European Society for Medical Oncology (ESMO) and European Society for Clinical Nutrition and Metabolism (ESPEN) to determine when escalation to enteral nutrition is required [35, 36]. The ESMO guideline for UGI cancers include considering enteral nutrition to maintain nutrition status when oral feeding (including the use of oral nutrition supplement drinks) is predicted to remain suboptimal [35]. The ESPEN guidelines recommend commencing enteral nutrition when there is suboptimal oral intake of less than 60% of estimated energy expenditure for greater than ten days, where the goal of EN would be to supplement oral intake to meet nutrition requirements [36]. Participants will be assessed for the need of a feeding tube at each dietitian consult and if deemed appropriate by the intervention dietitian, escalation to enteral nutrition will be discussed with the participant. Some participants may require a tube insertion at the commencement of the intervention due to previous substantial weight loss or deteriorating nutrition status. Participants are educated on their first assessment that they may also request this to occur prophylactically. If the participant agrees to an enteral feeding tube insertion, the participant’s primary health service gastroenterology team will be notified by the intervention dietitian to facilitate insertion. If a patient has a borderline resectable tumour, the treating surgeon will be consulted to ensure that tube insertion doesn’t interfere with the participant’s planned surgery. Participants will be supplied with the enteral formula; Abbott Vital^®^ 1.5 cal/mL, a peptide-based, partially hydrolysed, nutritionally complete formula [37]. Alternative formulations may be required as per the dietitian’s recommendation in consultation with the patient. As soon as practical after the feeding tube has been inserted a Home Care Nurse (healthcare company representative) will visit the participant (and/or their family and carers) at home or at their healthcare institution to provide training and education on using and caring for the feeding tube.

The enteral feeding regimen will be established in collaboration with the participant, to meet nutritional demands and to minimise interruptions to the participant’s lifestyle. Regimens will be adapted throughout the intervention phase, depending on changes in nutritional deficits, nutrition impact symptoms arising, weight loss and/or treatment stage. Enteral feeding can be delivered as a continuous or intermittent regime via a feeding pump, or bolus feeds, depending on participant preference and tolerance.

Feeding tubes will be removed at the end of the six-month intervention, unless it remains clinically indicated and a conversation regarding the continuation of feeding has occurred between the participant and their health care team. For participants who choose to continue enteral feeding post conclusion of intervention period, a handover to the nutrition team of the participant’s health service will be provided as they will be responsible for managing the ongoing nutrition care of patients who receive enteral nutrition at home.

#### Nutrition impact symptoms

All nutrition impact symptoms will be recorded for all intervention participants at each consult, and strategies to assist with the management of these will occur through goal setting, delivery of nutrition education and counselling, and recommended prescribed medications.

#### Pharmacological support

To help manage nutrition impact symptoms in a timely manner, all participants will be provided with a standard set of prescriptions upon commencing the study which will be sourced by the site liaison, including prescriptions for PERT (25,000IU microsphere capsules), metoclopramide (10 mg tablets), and ondansetron (8 mg tablets or wafers). The intervention dietitian will be able to guide participants on correct usage as per medical instructions of the prescribed medications to assist in preventing or relieving symptoms. Severity of PEI and the requirement for PERT will be assessed using the American Gastroenterological Association Guidelines, which involves screening for presence of symptoms such as bloating, gas, altered bowel motions, weight loss and steatorrhea [38]. Timing, dosage and correct administration of PERT will be guided by the dietitian in line with oral intake (including oral nutrition supplement drinks), symptoms and/or supplemental enteral feeding and will be re-assessed at each telehealth consultation with dosages/timing adjusted as required. PERT will be administered either orally or with enteral feeds using either a naso-jejunal tube (NJT), percutaneous endoscopic gastro-jejunal tube (PEG-J) or radiologically inserted gastro-jejunal tube (RIG-J). If required, the intervention dietitian may recommend that participants purchase over the counter medications such as aperients or anti-diarrhoeals. All other medications will need to be prescribed by the participants’ treating medical team or general practitioner e.g. opioid analgesics or antidepressants, and will be charted accordingly. The intervention dietitian will work closely with the participant’s treating medical team to escalate the need for further medications as required.

#### Psychological support

The intervention dietitian will complete a brief National Comprehensive Cancer Network (NCCN) Distress Thermometer score with participants at the first assessment and thereafter where deemed appropriate (i.e. where there appears to be a change in the participant’s mood or affect) [39]. Where required, with participant consent, the dietitian will determine the appropriateness of referrals to health service’s social work or psycho-oncology departments as per usual care. The Cancer Council telephone information and support service, SuicideLine and Lifeline phone numbers will be provided to participants at commencement of the study in the participant information pack. Urgent escalation of required psychological support may occur through contacting the area mental health services.

### Hospital admissions

Participants may be admitted to hospital for medical treatment during the intervention period, and may be seen by a dietitian within the local health service as part of usual care. The intervention dietitian will identify patients who have been admitted via the health services’ electronic medical records (EMR); alternatively, the participant may alert the intervention dietitian via phone or email. To ensure the continuum of care, detailed handovers will be provided to the dietitian at the health service by the intervention dietitian in a standardised ISBAR (identification, situation, background, assessment, and recommendation) format using a study developed proforma [40]. Upon discharge from hospital a handover will be provided back to the intervention dietitian.

### Adherence

If a participant misses a planned nutrition assessment or review, the intervention dietitian will make phone or email contact. The consult may be rescheduled or adapted to another telehealth means as required. Adherence to nutrition recommendations that impact on nutrition impact symptoms will be monitored by the intervention dietitian at each telehealth review.

### Data collection

Outcome data will be collected at baseline, three months and six months, in a manner preferred by the participants: either via phone with the blinded data collector, or self-completed via REDCap or email. Physical assessments will be carried out in person at the participant’s home, or their chemotherapy day unit at a time of their preference, by a blinded study data collector.

### Primary outcome

The primary outcome for this study is health-related QoL as measured using the summary score of the EORTC–QLQ-C30 at each follow-up time point [41]. This is a validated, reliable and widely used measure of health-related quality of life in oncology, palliative and supportive care research, including five functional subscales (physical, role, cognitive, emotional, and social) and with a range of domain-specific subscales available that capture symptoms of pancreatic cancer including pain, fatigue, nausea and vomiting, dyspnoea, insomnia, appetite loss, constipation, and diarrhoea [42]. The summary score is determined using the average of all the QLQ-C30 scale and item scores (as above) however not including global QoL and financial impact [43].

### Secondary outcome measures

QoL using the pancreatic cancer specific supplementary module, the EORTC-QLQ-Pan26, EQ-5D-5 L and 12-month mortality are secondary outcome measures [44, 45]. Presence of malnutrition and severity grading will be measured using the Patient Generated Subjective Global Assessment Short Form (PG-SGA_SF_), Global Leadership Initiative on Malnutrition (GLIM) Criteria, and ICD-10 [29, 42, 46]. These tools are commonly used globally to measure the nutrition status of oncology patients [29]. Weight will be assessed to help determine the impact of the intervention on the incidence/degree of weight loss, which is a negative indicator for treatment outcomes and survival [47]. Skeletal muscle mass will be assessed using the gold standard method of analysis of computed tomography (CT) imaging undertaken during routine clinical care at baseline and six months, and using muscle ultrasound and calf circumference at baseline, three months and six months. Low skeletal muscle mass is an independent prognostic indicator and is associated with dose-limiting chemotherapy toxicity [48, 49]. Skeletal muscle function will be assessed using measuring hand grip strength at baseline, three months and six months [50]. The Demoralization Scale–II, a well validated 16-item self-report measure, will be used to assess demoralization [51]. Chemotherapy dose reductions will be measured using relative dose intensity (RDI) which is the ratio of the delivered dose intensity (dose per unit of body surface area per unit of time) to the planned chemotherapy dose and this will be collected in the weekly dietitian consultations and/or through the EMR. An RDI below 85% is considered a clinically significant reduction from planned chemotherapy [52].

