**Fig. 2 Fig2:**
[figure not shown]
Study flow chart

The study flow chart depicts the two pathways; the intervention and usual care group. The usual care group will be screened for malnutrition at their healthcare services and will be referred to a dietitian when clinically indicated. Those in the intervention group will receive weekly telehealth dietitian interventions.

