### Randomisation and blinding

The random allocation sequence will be developed by a statistician who has no role in the recruitment of participants or data collection. Dynamic randomisation methods will be employed using STATA 18, based upon dichotomisation of malnutrition risk score at baseline assessment (Patient Generated Subjective Global Assessment Short Form (PG-SGA_SF_) score of < 12 vs. ≥ 12 based on distribution of baseline scores from our previous research) cancer stage (borderline resectable or locally advanced vs. metastatic), and commencement of chemotherapy (yes vs. no) [7, 28, 29]. The randomisation sequence will be generated by the study project managers and kept in a password-encrypted file. The project managers will contact the intervention dietitian and provide the sequential participant registration number. Participants will be informed of their group allocation via phone by the intervention dietitian.

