### ‘Usual care’ control group

Routine dietetic care will be received by those participants randomised to the control group, also known as usual nutrition care. Usual care most commonly involves nurse-led malnutrition screening at each chemotherapy visit or acute inpatient admission, with patients at risk of malnutrition referred to a dietitian for nutrition assessment and intervention to optimise nutrition status. The timing and delivery of usual care will differ between health services.

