### Database extraction

The intervention dietitians will have access to each hospital’s EMR to allow for data collection and collaboration with multi-disciplinary members to occur. Data extractions from MBS and PBS databases will be completed at the end of the trial where possible.

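### The rule for collecting relative dose intensity allows a data source that exists only in the intervention arm and is held by the unblinded intervention dietitian

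*Protocol article*

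**What the plan says.** The Secondary outcome measures section of the protocol article defines RDI as delivered dose intensity relative to planned dose, and gives its source: "this will be collected in the weekly dietitian consultations and/or through the EMR". It adds a threshold: "An RDI below 85% is considered a clinically significant reduction from planned chemotherapy". The abstract lists chemotherapy dosing changes among the secondary outcomes.

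The Fig. 2 caption describes dietitian contact in each arm. For the intervention: "Those in the intervention group will receive weekly telehealth dietitian interventions". For control: "The usual care group will be screened for malnutrition at their healthcare services and will be referred to a dietitian when clinically indicated". The section on the usual care group adds: "The timing and delivery of usual care will differ between health services".

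On who knows the allocation, Randomisation and blinding says: "Participants will be informed of their group allocation via phone by the intervention dietitian". On access to records, Database extraction says: "The intervention dietitians will have access to each hospital’s EMR to allow for data collection".

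**The concern.** An outcome compared between randomised arms should be ascertained in the same way in both. Here one of the two named sources is the intervention contact itself. An intervention participant may contribute weekly reports for six months, the record, or both, while a control participant can contribute only the record. A telehealth conversation and a chemotherapy chart are not interchangeable sources for a ratio that needs dose, body surface area, time and planned dose. The person taking the conversational data also delivers the treatment.

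At stake is the interpretation of any difference in RDI. Better dose delivery is one of the benefits the Background proposes, and dose reduction is its example of how symptoms and malnutrition shorten survival. If RDI were counted among the mechanistic outcomes in the mediation analysis, the same measurement problem would carry into it.

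**Working it through.** The document gives no RDI figure to reproduce, and the sample size calculation concerns the primary outcome only. The check is therefore mainly a comparison of sections.

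1. **Sources by arm.** Permitted sources are the consultation, the EMR, or both. Intervention arm: consultations are weekly for six months, about 6 × 52/12 = 26 contacts, plus the EMR. Control arm: no weekly study consultation, and referral only if clinically indicated, with site-dependent timing. The control arm is left with the EMR.

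2. **Blinding of the consultation source.** The intervention dietitian tells participants their group and runs the consultations. RDI information taken there is collected unblinded.

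3. **Blinding of the EMR source.** Intervention dietitians have EMR access for data collection. The section does not mention RDI or control participants, and does not say that nobody else extracts data. Who extracts control-arm RDI is not stated.

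4. **Does another section correct this?** Data collection describes a blinded collector or self-completion at baseline, three and six months, which does not match weekly collection by a dietitian. Blinded outcomes promises blinded collection and analysis for the quality-of-life primary outcome only. Neither gives RDI a common source.

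5. **Possible size, by assumption only.** Let p be the true share with RDI below 85%, equal in both arms, and let s1 and s0 be the probabilities that such a participant is recognised in the intervention and control arms. Ignoring false positives, the spurious difference is p × (s1 − s0).
   - p = 0.3, gap 0.10: 3 points
   - p = 0.5, gap 0.10: 5 points
   - p = 0.7, gap 0.10: 7 points

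   If s0 exceeds s1, the sign reverses. For scale, the standard error of a difference in proportions near 0.5 with 41 per arm is √(2 × 0.5 × 0.5 / 41) = 0.110, or 11 points. None of p, s1 or s0 comes from the document.

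**The case against.** The strongest reply is that the wording allows EMR collection for every participant. Consultation reports might only prompt a check of the record, and the extractor may be named in the full protocol that the article condenses. This stands in part, and it rules out several stronger readings that a reader might infer.

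- **That RDI is measured differently by arm and the comparison is biased.** The text permits this and does not require it.
- **That all RDI data are collected by unblinded staff.** This is established only for data taken at consultations. The dietitians' EMR access also serves their clinical role, such as identifying hospital admissions.
- **That the bias runs against the intervention by a particular amount.** Closer contact could uncover more reductions in that arm, and an unblinded collector could err the other way. Detection rates are nowhere given. RDI is a ratio, not an event found or missed, and the Data analysis section specifies no comparison at the 85% threshold. The illustrated differences are also smaller than one standard error, although a systematic difference does not shrink as numbers grow.
- **That records are patchy at some sites.** The document does not say so.

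What remains is that the article does more than leave a detail open. It states a source rule, and that rule names a source available to one arm only.

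**Conclusion.** The point holds as a weakness in a stated rule: RDI may be drawn from different sources by arm, and one of those sources is unblinded. This leaves the between-arm comparison open to ascertainment bias of undetermined direction and size. The conclusion rests on the article's own description of the two arms and on no numerical assumption. The 3 to 7 points are illustrative and depend entirely on the assumed detection gap and prevalence. The quality-of-life primary outcome and the sample size are not affected. Because RDI is a secondary outcome and the remedy is cheap, the change should be made, but the trial's main conclusion does not depend on it.

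**What to change.** State that RDI in both arms is derived from one common source, namely chemotherapy administration or pharmacy records in the EMR. Use the same window from randomisation and the same calculation in both arms. A common start matters because some participants will already have had one cycle at entry. State that doses or delays reported in consultations are not used for this outcome; they can still serve clinical care.

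Where feasible, calculate RDI from a chemotherapy-record extract that does not show allocation, handled by someone other than the treating dietitian. Do not give the blinded outcome collector full EMR access for this purpose. Dietitian handovers or tube-insertion requests, if filed there, could reveal the arm to the person who takes the phone and physical outcomes.

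The cost is a wording change and reassignment of one extraction task. Dose information reported only in consultations goes unused. Some chemotherapy given outside the participating hospitals' records may be missed, but under the same rule in both arms. Treatment and sample size do not change.
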